## Abstract

**Aims:**

Syncope is responsible for 1–3% of emergency department presentations. The European Society of Cardiology guidelines on syncope recommend a structured initial evaluation to diagnose syncope patients. If the cause of the syncopal event remains unexplained, risk-stratification is applied to distinguish between patients at high risk of serious cardiovascular events and low-risk patients, who can be safely discharged. However, there is a group of patients in whom this risk can currently not be adequately determined, hereafter called intermediate risk. In clinical practice, these patients are either immediately discharged or admitted for 24 h in-hospital cardiac rhythm monitoring. Due to the high cost of admission, immediate discharge could lower healthcare costs, hospital bed utilization, and patient burden. To our knowledge, there is no sufficient scientific basis for the superiority of either. The RISC trial aims to resolve this knowledge gap.

**Study Design:**

The RISC trial is an investigator-initiated multicentre prospective randomized controlled trial. A total of 640 predefined low- and intermediate-risk syncope patients are randomized to either immediate discharge or discharge after 24 h in-hospital rhythm monitoring (1:1). The trial is powered to claim non-inferiority of immediate discharge with respect to (non-)fatal composite safety endpoints, which entail arrhythmic disorders, syncope recurrence, and (cardiovascular)death. Furthermore, healthcare costs and quality of life will be evaluated.

**Conclusion:**

The RISC trial is a multicentre RCT that aims to gather scientific evidence for immediate discharge of the ESC guideline–based pre-defined low- and intermediate-risk syncope patients in the emergency department. Primary endpoints entail cardiovascular events such as arrhythmias, syncope, and death. This trial is registered at ClinicalTrials.gov with trial-ID: NCT06472375.

## Background

Syncope is defined as a transient loss of consciousness (TLOC) due to global cerebral hypoperfusion.^1^ Each year, one in every thousand inhabitants presents in the (cardiac) emergency department ((C)ED) with syncope,^2^ accounting for 1–3% of emergency department presentations.^3^

Syncope is a symptom with a broad differential diagnosis, spanning across the lines of medical specialties (cardiology, neurology, internal medicine, geriatrics, emergency medicine, and primary care). Additionally, causes range from benign to life-threatening. The combination of a diverse differential diagnosis spanning multiple specialties, mostly based on circumstantial evidence to establish a diagnosis on, and time constraints in emergency departments makes the evaluation of syncope patients challenging for most physicians.^4^

If the initial evaluation yields a certain/highly likely diagnosis, treatment is instigated based on the cause of the syncopal event. Cardiac syncope patients should be admitted for treatment and additional diagnostic evaluation, as they are at substantial risk of serious cardiovascular events. In contrast, patients with evident reflex syncope and orthostatic hypotension (autonomic syncope) can be safely discharged, as they do not benefit from hospital admission or observation for the diagnosis or treatment of the syncopal event.^1,5–9^

There is, however, a significant group in whom the origin of syncope is still unexplained after the initial evaluation. In these patients, the 2018 European Society of Cardiology (ESC) guideline recommends risk stratification.^1^ The ESC guideline provides high-risk features in the scope of history taking, physical examination, and 12-lead electrocardiogram. These risk features are used to stratify patients into low (no high-risk features) or high risk (multiple risk features) of serious cardiovascular events. In earlier studies, eventually adjudicated cardiac patients were adequately identified using the ESC-guideline based initial evaluation, exhibiting the safety of the guideline-based structured evaluation.^5,10–12^ The guideline recommends discharge of low-risk patients, which includes mostly patients with either suspected reflex syncope or suspected orthostatic hypotension (autonomic syncope), and admission of high-risk patients (suspected cardiac syncope).^1^ However, the management of patients in whom the risk is undetermined, hereafter called intermediate-risk patients, is not yet defined. Management in this group is precarious, as the high-minor risk feature (*Table 1*) often warrants suspicion of a cardiac culprit, but not enough to definitively require admission. The discrimination between admission and discharge in intermediate-risk patients is therefore subjective in nature, leading to heterogeneous treatment strategies across healthcare providers and potentially unnecessary admissions of suspected autonomic syncope patients. This is problematic as admission is the primary driver of syncope-related costs.^13^

**Table 1 oeag078-T1:** Features for risk stratification

[figure not shown]

AF, Atrial fibrillation; ARVC, Arrhythmogenic Right Ventricular Cardiomyopathy; AV block, Atrio-ventricular block; BP, Blood pressure; ED Emergency department; IVCD, Intraventricular conduction disorder; LBBB, Left Bundle Branch Block; LVH, Left Ventricular Hypertrophy; LQTS, Long QT Syndrome; SCD, Sudden cardiac death; SVT, Supra ventricular tachycardia; VT, Ventricular Tachycardia

## Rationale

The current reason for the admission of syncope patients is two-fold. First, admission is considered safe because, in the case of rhythm disorders, immediate treatment can be started. Second, admission for monitoring may provide additional diagnostic value, given the chance of witnessing recurrence during the first hours after the syncopal event.^14^ Therefore, the question posed for intermediate-risk syncope patients is two-fold as well: is it safe to discharge these patients, and does admission provide a diagnostic benefit? If intermediate-risk patients can be safely discharged but might profit from rhythm observation, the solution of immediate discharge combined with immediate ambulant Holter monitoring could greatly reduce healthcare costs. Similarly, if there is no diagnostic yield, ambulant Holter monitoring could be omitted as well.

Therefore, we propose the RISC trial to investigate the safety of immediate discharge and the clinical benefit of ambulatory Holter monitoring in low- and intermediate-risk syncope patients. Furthermore, it evaluates the true healthcare cost benefit, the effect on the quality of life, the societal costs, and healthcare burden from a patient perspective. Additionally, we aim to investigate the diagnostic efficacy of immediate rhythm observation and, if apparent, the optimal duration of ambulatory Holter monitoring. The RISC trial, therefore, aims to determine whether immediate discharge with or without ambulatory Holter monitoring is safe and if it is a clinically and economically appropriate alternative to 24-h in hospital cardiac rhythm monitoring in pre-defined low- and intermediate-risk syncope patients.

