### Randomization

Upon inclusion, participants will be randomized to either the intervention arm (immediate discharge) or the comparator arm (24-h telemetry monitoring). Randomization is performed using a web-based weighted variable block design. Both study arms will receive 5-day ambulatory Holter monitoring upon randomization in order to record endpoints with the same modality. Physicians are advised to manage these patients as they would following the local protocols, with as the only confining factors being the minimal 24-h observation period and cardiac rhythm observation.

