### Holter monitoring

Immediately after randomization, both treatment arms will receive 5-day ambulatory Holter monitoring using the Philips ePatch®.^16^ Patients are required to wear the Holter for a minimum of 24 h with sufficient signal. Holter patches are reapplied when they are not securely fixated during the first 24 h to ensure complete registration in the first 24 h for the primary endpoint analysis. After the initial 24-h period, Holter patches are not reapplied. All Holter recordings are analysed using the Cardiologs Holter analysis platform by an experienced clinician, a second expert will perform an independent quality control review.^17^ All pre-defined rhythm disturbances will be reported (Appendix C), even if they are not part of the endpoints. In the event of clinically relevant findings, treating physicians are notified immediately. The ambulatory Holters are not monitored in real time, as not to affect healthcare costs. Treating physicians will not have standard access to the full Holter report; the Holter data are available on request, allowing researchers to assess the potential diagnostic yield of the Holter monitoring.

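### The stated aims cover discharge without Holter and the clinical benefit of Holter, but every patient in both arms wears one, so the design has no contrast for either

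*Protocol article*

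**What the plan says.** The protocol article sets two Holter-related aims in its Rationale. The trial is to "investigate the safety of immediate discharge and the clinical benefit of ambulatory Holter monitoring in low- and intermediate-risk syncope patients", and it "aims to determine whether immediate discharge with or without ambulatory Holter monitoring is safe". The same section gives the reasoning behind the second part: "if there is no diagnostic yield, ambulant Holter monitoring could be omitted as well".

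The Trial design section describes two arms, immediate discharge and 24-h in-hospital rhythm observation. The Randomization section adds: "Both study arms will receive 5-day ambulatory Holter monitoring upon randomization in order to record endpoints with the same modality".

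The Holter monitoring section says that nobody watches the recordings live and that physicians do not routinely see the complete report but may ask for the data. It also says: "In the event of clinically relevant findings, treating physicians are notified immediately".

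The Endpoints section places the primary composite at 24 h. Among the secondary endpoints are the diagnostic yield of Holter, admission costs, tests and consultations after 1 month, and the proportion of correct diagnoses.

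**The concern.** Judging discharge with and without Holter, or the clinical benefit of Holter, needs patients who differ in whether they have one. This trial has none. Nor is the Holter a purely silent measuring device, because relevant findings can reach the physician in either arm.

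What is at stake is the claim that the trial may make. The Conclusion of the Abstract speaks of evidence for immediate discharge, and the Summary asks whether the 24-h admission can be left out safely. Neither says that every discharged patient also had a 5-day Holter with notification. Together with 'or without' in the Rationale, a noninferior result could be taken as direct evidence for plain discharge. The Rationale treats discharge with Holter and discharge without it as different policies with different costs, so the distinction matters to the trial's own question.

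**Working it through.** **1. What the sample size covers.** Inputs from Statistical considerations: event rate 18% in both arms, margin 9 percentage points, one-sided alpha 0.025, power 80%, 10% loss; 1:1 allocation from the Abstract.

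- Unpooled variance: n per arm = (1.960 + 0.842)² × 2 × 0.18 × 0.82 / 0.09² = 7.849 × 0.2952 / 0.0081 = 286.05, rounded up to 287. Total 574; 574 / 0.90 = 637.8, so 638.
- Farrington–Manning variance, with restricted rates of 0.143 and 0.233 under the null: 290.5 per arm, 581 in total; 581 / 0.90 is about 645.
- Power with 576 evaluable patients (640 × 0.90, 288 per arm): standard error = √(0.2952 / 288) = 0.0320; 0.09 / 0.0320 − 1.960 = 0.851; power 80.3%.

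The stated 640 reproduces. All of this power belongs to discharge against observation, with Holter in both arms.

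**2. Which strategies are observed.**

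| Strategy | Patients allocated (of 640, 1:1) |
|---|---|
| Discharge, with Holter | 320 |
| 24-h in-hospital monitoring, with Holter | 320 |
| Discharge, without Holter | 0 |
| 24-h in-hospital monitoring, without Holter | 0 |

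**3. Which questions that identifies.** Write R(d, h) for the mean outcome under discharge (d = 1) or observation (d = 0), with Holter (h = 1) or without (h = 0).

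- R(1,1) − R(0,1), discharge against observation with Holter in both: estimated by randomization.
- R(1,0) − R(0,0), or R(1,0) − R(0,1), the safety of discharge without Holter: R(1,0) is never observed.
- R(1,1) − R(1,0), the clinical benefit of Holter in discharged patients: R(1,0) is never observed.
- Proportion of wearers with a clinically relevant finding: estimable in both arms, with no need for a no-Holter group.

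Moving from the first line to the second requires R(1,1) to be close to R(1,0), and R(0,1) close to R(0,0) if the comparator too has no Holter. In words, wearing the Holter must not change the outcome by the time it is assessed.

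**4. How plausible that is, by outcome.**

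- *Primary composite at 24 h.* Holter can alter it only if a finding is read, notified and followed by a change of care within 24 h. Without live monitoring that is probably uncommon. This is an inference: the article gives no reading or notification times and lets physicians request the data.
- *Secondary outcomes after reading.* Tests and consultations after 1 month, costs and correct diagnoses can include care that follows a notification. For diagnosis, the comparison is telemetry plus Holter against Holter alone. A shared rhythm record would plausibly make the arms more alike, but the documents give no figure from which to size this.

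**5. What yield can and cannot settle.** A negligible yield would support leaving the Holter out, as the Rationale argues. A positive yield would not show whether finding and reporting those rhythms helps patients.

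**The case against.** The strongest defence is that the Holter question rests on diagnostic yield, a named secondary endpoint that is best measured when everybody wears the device. Universal Holter also has a sound purpose: it records endpoints in the same way at home and in hospital, which protects against unequal detection between arms. Physician access is deliberately restricted. The operative objective in Trial design, the Abstract and the Summary contain neither 'or without' nor clinical benefit. All of this stands. It makes the point one about wording and claim, not about the choice to fit a Holter to everyone.

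A reader might infer more than the documents support:

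- *That neither Holter question can be informed at all.* Yield is estimable, and a null yield is the protocol's own route to omitting Holter. What is missing is a randomized contrast.
- *That every patient receives feedback which is then acted on.* Every patient wears a Holter, but notification follows only a relevant finding. The text says that physicians are told, not what they do next.
- *That the noninferiority test is compromised.* It applies to the 24-h composite, which live-unmonitored recordings can hardly influence.
- *That shared Holter care tilts the trial towards its hoped-for result.* For costs and tests the hope is a saving, so a smaller contrast would be conservative.

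The defence does not rescue the two aims as worded. Yield describes findings and is not an effect on outcomes. The extension of the 24-h result to discharge without Holter rests on an assumption that the article does not state.

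**Conclusion.** The two Holter aims in the Rationale are wrong as written. The design allocates 0 of 640 patients to no Holter, so the safety of discharge without Holter has no direct evidence and the clinical benefit of Holter cannot be estimated. Diagnostic yield can be.

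The sample size, margin and primary analysis are unaffected, and the question of discharge against 24-h observation, with Holter in both arms, is properly randomized. The 24-h result may bear in part on discharge without Holter-guided care, on the assumption that little care triggered by Holter occurs before 24 h. Secondary outcomes assessed after reading describe strategies that include Holter with notification. The size of any effect on them cannot be worked out from the documents.

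**What to change.** - Restate the aim and the conclusion as immediate discharge with 5-day ambulatory Holter against 24-h in-hospital monitoring with the same Holter. This concerns the Rationale and the concluding statements in the Abstract and Summary, which should name the Holter.
- Replace clinical benefit by diagnostic yield in the Rationale.
- Either delete 'or without', or state the assumption under which the result extends to discharge without Holter: negligible care triggered by Holter before 24 h for the primary endpoint, or negligible yield.
- If the assumption is kept, support it with descriptive counts, by arm and by time from randomization, of notifications and of the changes of care that followed. Enrolment is under way, so these are best captured prospectively. The full protocol may already provide for them.
- Do not present an analysis that removes care triggered by a notification as a no-Holter comparison. It conditions on events after randomization and does not recover what would have happened without the device.

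The cost is text changes, a short descriptive table if the extension is kept, and a narrower claim. Arms, sample size and primary analysis stay as they are.

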## Trial design

The RISC syncope trial is an investigator-initiated, multicentre, randomized, controlled, prospective two-arm clinical trial designed to evaluate if immediate discharge is noninferior to in-hospital 24-h cardiac rhythm observation. Patients are identified in the (cardiac) emergency departments of 10 large teaching hospitals (two academic and eight nonacademic) in the Netherlands. All syncope patients presenting to the (C)ED are analysed using the initial evaluation as described in the 2018 ESC guidelines on syncope within the first 4 h after arrival in the (C)ED. The guideline-based initial evaluation consists of thorough history taking, physical examination, active standing test, and a 12-lead electrocardiogram (*Figure 1*) and is part of standard care in the (C)ED in all participating hospitals.

**Figure 1 oeag078-F1:**
[figure not shown]
Trial design flowchart.

### Patient selection

If the initial evaluation yields a highly likely or certain diagnosis of autonomic syncope (low-risk diagnosis), patients are screened for enrolment. The distinction between low or intermediate risk for subgroup analysis is then made using the ESC guideline–based RISC score (see next paragraph).

Patients in whom no highly likely or certain diagnosis can be established (unexplained diagnosis), ESC guideline–based RISC stratification will be performed (see next paragraph). Low- and intermediate-risk syncope patients are screened for enrolment.

Before enrolment, patients are screened using the inclusion and exclusion criteria (*Table 2*).

**Table 2 oeag078-T2:** Inclusion and exclusion criteria

*Inclusion criteria*
All low and intermediate cardiac risk syncope patients on the (C)ED
>18 years old
Able to provide informed consent
*Exclusion criteria*
Those aged <18 years Stratification as high risk
Contraindication for early discharge Certain or highly likely cardiac diagnosis Illness Trauma Social
Near-syncope
Unable to provide informed consent Unable to fill in questionnaires

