### Risk stratification: ESC guideline–based RISC score

Patients will be risk-stratified using the pre-defined ESC guideline–based RISC score (*Figure 2*). This score is calculated by assigning 1 point to every high-minor feature and 2 points to every high-major feature (*Table 1*). All patients will then be classified in three groups: low- (0 points), intermediate- (1 point), and high-risk (2 points) of serious cardiovascular events (*Figure 2*). Additionally, patients with a low calculated risk but with ≥1 high burden feature are deemed intermediate risk; these features include trauma without admission indication, high symptom burden, documented 1A/1B asystole during a reflex syncope, or a combination with functional transient loss of consciousness (psychogenic pseudosyncope) (see *Table 1*).

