### Endpoints

The primary safety endpoint consists of the composite of arrhythmia disorders (supraventricular tachycardia, sinus pauses or bradycardia, and ventricular tachycardia), pre-defined conduction disorders (second- or third-degree AV block), syncope recurrence, unexplained falls with injury, all-cause death, and cardiovascular death (Appendix B) at 24 h after randomization. All primary endpoints will be evaluated at 24 h. Subgroup analysis will be performed on the low-risk and intermediate-risk–only cohorts.

Secondary endpoints include clinically relevant diagnostic yield of Holter monitoring, total admission costs, number of syncope-related tests and consultations after 1 month, duration of in-hospital stay after randomization for both treatment arms (superiority), and differences in proportion of correct diagnoses in both arms. In addition, quality of life and societal costs are assessed using telephone consults and standardized questionnaires of the SF12, SDF, EQ-5D-5L, and study-adapted iMCQ and iPCQ (Appendix A). Although quality of life (measured as QALYs) may not differ due to the risk of the population closely resembling a normal population, there might be a difference in perceived safety and understanding affecting the quality of life indirectly.

All primary endpoint definitions are described in Appendix B. A critical event committee centrally reviews all events that are potential endpoints.

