### Statistical considerations

Immediate discharge (Intervention) is compared with discharge after 24-h in-hospital observation with rhythm monitoring (Comparator). We chose a prospective analysis due to the patient and physician bias, which would be inherent to a retrospective design. By application of 5-day ambulant Holter monitoring for all participants, we are able to compare all (non-)fatal events in both arms for which admission is strictly not mandatory (e.g. nonrhythm issues and/or later timing of nonfatal diagnoses). Based on studies on low- and intermediate-risk syncope patients in the setting of ED and in line with data from our own institute, we anticipate an event rate of 18% in both arms.^14,18–33^ By noninferiority, we aim to show that immediate discharge of these low-/intermediate-risk syncope patients is feasible and safe. With a noninferiority limit of 9% (for the difference in event rates, 50% of 18%), inclusion of a total of 640 patients with a one-sided type-1 error of 0025 provides the trial with 80% power (10% loss included). In the RISC trial, the noninferiority margin for the risk difference was set at 9% against an expected event rate of 18%, or half of the expected event rate. This margin is equivalent to a noninferiority margin of 1.50 for relative risk. The RISC trial’s noninferiority boundary is consistent with choices made for major landmark RCTs that influenced current guidelines (examples of RCTs are available upon request). In general, the choice of the noninferiority boundary has a major impact on the sample size needed for adequate power. A stricter noninferiority boundary would necessitate an impractically large sample size. For example, a noninferiority margin of 6% against an expected event rate of 18%, equivalent to a relative risk margin of 1.33, would more than double the sample size to 2 × 644. For the inclusion rate, based on the reference areas of the participating hospitals, the annual admissions of syncope on the emergency department, this will result in ≈ 50 eligible patients per year per centre.

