### Data analysis and bias

The main analysis is designed to evaluate whether immediate discharge (investigational treatment strategy) is noninferior to 24-h admission with continuous rhythm observation (reference treatment strategy) with respect to the primary composite endpoint of fatal and nonfatal events. The occurrence of the composite primary endpoint will be analysed in a statistical comparison of two proportions of (non-)fatal events. Rates of the primary endpoint are calculated as the proportion of patients in whom the primary endpoint has occurred. Rate differences are defined as the rate under the investigational treatment strategy minus that under the reference treatment strategy. The 95% confidence interval for the rate difference is calculated according to the Farrington–Manning method. Noninferiority of the investigational strategy of immediate discharge will be declared if the 95% confidence interval for the rate difference excludes 9%. Use of 95% confidence interval is equivalent to noninferiority testing with a one-sided type I error (α) of 2.5%. The one-sided *P* value for testing noninferiority with a margin of 9% is calculated according to Farrington–Manning method and must < 2.5% for rejection of the null-hypothesis of inferiority.

All of the analyses are carried out in the population of all randomized patients under application of the intention-to-treat principle, which implies that all primary endpoints are counted irrespective of the implementation of the randomized treatment assignment.

The follow-up period for each patient begins on the day of randomization and will be as long and continues for up to 12 months, with the aim of complete data collection. It is expected that the occurrence of the primary endpoint at 24 h will be known for all patients, except for those patients with early discontinuation of follow-up because of full withdrawal of informed consent.

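### The powered test covers a mixed low- and intermediate-risk population; a pass does not by itself establish safety in intermediate-risk patients, whose subgroup analysis has no margin or claim rule

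*Protocol article*

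**What the plan says.** **Where the uncertainty lies.** The Abstract (Aims) describes low-risk patients as safe to discharge and names the group of undetermined risk as the gap the trial is to close. The Background says that "the management of patients in whom the risk is undetermined, hereafter called intermediate-risk patients, is not yet defined", and the Rationale poses its two-part question about that group. Of evident autonomic syncope, the Background says that "patients with evident reflex syncope and orthostatic hypotension (autonomic syncope) can be safely discharged, as they do not benefit from hospital admission or observation"; it also reports that the guideline recommends discharging low-risk patients.

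**Who is enrolled.** Both risk groups are eligible. Under Patient selection, "If the initial evaluation yields a highly likely or certain diagnosis of autonomic syncope (low-risk diagnosis), patients are screened for enrolment"; the next sentence has the RISC score class these patients as low or intermediate. One point means intermediate risk. In addition, "patients with a low calculated risk but with ≥1 high burden feature are deemed intermediate risk". The four burden features are trauma without an indication for admission, high symptom burden, documented asystole during reflex syncope, and functional transient loss of consciousness.

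**What is tested.** Under Statistical considerations, "we anticipate an event rate of 18% in both arms", with a 9-point margin, 640 patients and 80% power after 10% loss. Data analysis and bias applies this test to all randomized patients and adds: "Use of 95% confidence interval is equivalent to noninferiority testing with a one-sided type I error (α) of 2.5"%. On risk groups, the Endpoints section says: "Subgroup analysis will be performed on the low-risk and" intermediate-risk-only cohorts. It attaches no margin and no rule for a claim.

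**The declared aim.** The Abstract, the Rationale and the Summary all name low- and intermediate-risk patients together. The Summary says the guidelines leave the timing of discharge open for both.

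**The concern.** The rationale and the primary test differ in emphasis. The rationale puts the uncertainty mainly in one group, while the test averages over two.

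In a non-inferiority trial the direction of this averaging matters. Patients in whom the two strategies do not differ pull the pooled difference towards zero, and so towards a pass. If low-risk patients are such patients, an excess in intermediate-risk patients is scaled down by their share of the sample before it meets the margin.

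What is at stake is the wording of the conclusion. A pooled pass with an inconclusive intermediate-risk estimate would not close the gap described in the Abstract, and nothing in the article says how such a result is to be reported.

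The intermediate-risk group is also not uniform. It joins patients with one cardiac point to patients with no points and a burden feature, so its estimate needs to be shown by route of entry.

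**Working it through.** **Inputs from the article:** event rate 18% in both arms; margin 9 points; one-sided alpha 2.5%; power 80%; 640 patients randomized 1:1; 10% loss.

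**Not given, so assumed:** the intermediate-risk share w (shown at 75%, 50% and 30%); a reference rate of 18% in each risk group; no excess in low-risk patients.

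**1. The plan's own figures.** n per arm = (1.96 + 0.8416)² × 2 × 0.18 × 0.82 / 0.09² = 7.849 × 0.2952 / 0.0081 = 286.05, rounded up to 287. The total is 574, and 574 / 0.9 = 638, against 640 stated. With a 6-point margin the same formula gives 7.849 × 0.2952 / 0.0036 = 643.6, that is 644 per arm, as stated. The sample size is right for the pooled question. Evaluable patients per arm: 640 × 0.9 / 2 = 288.

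**2. Dilution.** With no low-risk excess, pooled excess = w × intermediate-risk excess. A pooled excess equal to the 9-point margin then corresponds to an intermediate-risk excess of 9 / w: 12 points at w = 75%, 18 at 50% and 30 at 30%.

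**3. Probability of a pooled pass when the intermediate-risk excess is 9 points.** P = Φ((0.09 − 0.09w) / SE − 1.96), with SE² = [p(1 − p) + 0.18 × 0.82] / 288 and p = 0.18 + 0.09w.

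| w | pooled excess | SE | P(pooled pass) |
|---|---|---|---|
| 100% | 9.0 points | – | 2.5% |
| 75% | 6.75 points | 0.0340 | 9.7% |
| 50% | 4.5 points | 0.0334 | 27.0% |
| 30% | 2.7 points | 0.0329 | 48.2% |

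**4. Power of the same test in intermediate-risk patients alone, with no true difference.** Power = Φ(0.09 / √(0.2952 / m) − 1.96), with m = 288w per arm.

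| w | m per arm | power |
|---|---|---|
| 75% | 216 | 68.2% |
| 50% | 144 | 51.1% |
| 30% | 86 | 33.6% |

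**5. Check with the planned method.** The Farrington–Manning statistic gives pooled-pass probabilities of 9.7% (w = 75%) and 26.8% (w = 50%); simulation with 40,000 runs gives 9.6% and 26.6%. Intermediate-only power by Farrington–Manning is 67.5% and 50.3%. The 30% row rests on the normal approximation only.

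**6. Sensitivity.** If the groups have different rates, intermediate-only power falls further. For example, at w = 50% a low-risk rate of 12% implies an intermediate-risk rate of (0.18 − 0.5 × 0.12) / 0.5 = 24%. The required number is then 7.849 × 2 × 0.24 × 0.76 / 0.0081 = 353.5, that is 354 evaluable per arm instead of 287. In the other direction, any true excess in low-risk patients would lower the pass probabilities in step 3.

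**The case against.** The strongest reply is that the pooled population is the declared target. The Abstract, the Rationale and the Summary name both risk groups, and the Summary says both are in practice either discharged at once or monitored. The primary test answers that question. This stands, and it rules out several stronger readings:

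- **That the type I error is inflated from 2.5% to 27%.** It is not. The 2.5% holds for the mixed population that the test names. The 27% is the chance of a pooled pass when a different hypothesis, about intermediate risk alone, is at its margin.
- **That the protocol says all low-risk patients gain nothing from admission.** Only the Background says this, and only of evident autonomic syncope. For low-risk patients generally, the documents say that they can be safely discharged and that the guideline recommends discharge. Zero low-risk excess is therefore an assumption here, not a stated fact.
- **That patients with an autonomic diagnosis are simply the low-risk group.** The score can class them as intermediate. The pooling itself is set under Statistical considerations and Data analysis and bias.
- **That the intermediate-risk result will go unreported.** A subgroup analysis is planned.
- **That burden-only patients have no bearing on rhythm outcomes.** One burden feature is documented asystole, and asystole of more than 3 seconds is a component of the primary endpoint in Appendix B.

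A second reply is that ranking and claim rules belong in an analysis plan that is not shown. That is fair, and if it already holds such a rule, the first change below is done. But the article does fix the pooled population, the margin and the sample size, and those choices alone support only a conclusion about the mixed population.

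**Conclusion.** The point holds as a limit on what may be concluded. The pooled test is correctly sized and valid for the mixed low- and intermediate-risk population. It does not by itself show that immediate discharge is safe in intermediate-risk patients, where the rationale mainly places the uncertainty.

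The size depends on a share and on group-specific rates that the article does not give. The range of about 10% to 48% for a pooled pass despite a 9-point intermediate-risk excess is therefore an illustration, as is the range of about 68% down to 34% for intermediate-only power. Both rest on 18% in each risk group; the first also needs no low-risk excess. The qualitative conclusion needs only that the excess may differ between the risk groups.

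**What to change.** 1. **Claim rule.** Keep the pooled primary test. If it passes, test the intermediate-risk difference against the same 9-point margin with a 95% confidence interval, as first key secondary endpoint. Claim non-inferiority for intermediate risk only if this passes; otherwise limit the conclusion to the mixed low- and intermediate-risk population. The fixed order costs no alpha and no patients. The downside is power: the figures above are upper bounds for passing both tests, so the claim may be inconclusive at 640 patients and must then be reported as such. Full power for intermediate risk at an 18% rate would need about 640 / w patients in total, for example 854 at w = 75% or 1,280 at w = 50%; that is not proposed here.
2. **Description.** Within intermediate risk, show patients with one cardiac point separately from those classed there by a burden feature alone (all four features), without a formal test.
3. **Precision, as a separate matter.** Estimate the primary marginal risk difference stratified by risk group and adjusted for age, keeping the 9-point margin. Risk group is assigned before enrolment and age is a listed baseline item. An assumed 5–10% reduction in variance would raise power from 80% to about 82–84%. This does not address dilution, and it changes the interval method named under Data analysis and bias, so it must be fixed before results are seen.

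All three are analysis-plan wording. The Summary says the trial is still enrolling, so they can be settled in time.
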